### Criteria for interrupting study participation

2.10

The number of participants interrupting participation, together with the reasons, will be registered and appropriately reported.

#### Abandonment by the participant

2.10.1

Any participant may leave the study at any time without having to give an explanation and without any consequence to the medical care or treatments received by any agent related to the study.

#### Interrupting participation by the researcher

2.10.2

The research team may discontinue any patient's participation (a withdrawn participant) at any time, provided that their participation poses a risk to their safety or a violation of the study protocol. This can occur under the following circumstances:

-Severe skeletal muscle injury that alters one's normal lifestyle (as a consequence, or not, of participating in the study).-Pregnancy during the intervention period. Alterations in the hormonal profile that occurs during pregnancy would irredeemably affect the study results.-A change of residence, making all postoperative assessments impossible.-Death.

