### Patient safety

2.9

For the entire study period, any possible adverse effects attributable to the intervention will be reported. An adverse effect in the EG is defined as any skeletal muscle injury that occurs during (or as a result of) the training performed.

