### Statistical analysis

2.11

Despite randomization, the between-group baseline comparability will be checked. Normal distribution of continuous quantitative variables will be graphically inspected using histograms, and—when needed—normality tests will also be used. The between-group differences in the change (post–pre) in the primary and secondary effects (the main and secondary objectives 1, 2, and 3) will be analysed using a general linear model (in the case of significant deviation from normality, we will proceed with non-parametric techniques, such as quantile regression). The effect size (95% confidence interval) and the level of statistical significance will be displayed. In order to demonstrate the clinical efficacy of the supervised exercise program on ovarian function after bariatric surgery, the main analysis will be a per-protocol analysis (i.e., it will only include participants who attend at least 80% of the exercise sessions). Sensitivity analyses will be carried out using the intention-to-treat principle to check the robustness of the results. Missing data will be replaced using multiple account imputation. Despite the randomization, we will attempt to minimize potential confounding by adjusting for baseline values and other potential confounders. The association between changes in ovarian function with changes in the mechanisms involved (secondary objectives 4, 5, and 6) will be analysed using Pearson or Spearman correlations and/or regression analysis. The analyses will be conducted with Stata v.13.1 or superior (StataCorp LP, College Station, TX). Statistical significance will be set at *P* < .05.

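### Researcher-initiated withdrawal does not separate stopping exercise from leaving follow-up, so avoidable missing outcomes could weaken the intention-to-treat analysis

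*Protocol article*

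**What the plan says.** Section 2.10 concerns interruption of study participation. Voluntary departure has its own subsection (2.10.1). Section 2.10.2 covers decisions by the researchers, who may withdraw any woman, in either arm and at any point, "provided that their participation poses a risk to their safety or a violation of the study protocol". Four circumstances follow:

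- injury, worded as "Severe skeletal muscle injury that alters one's normal lifestyle (as a consequence, or not, of participating in the study"
- conception, worded as "Pregnancy during the intervention period", with the reason that hormonal changes would affect the results
- relocation, worded as "A change of residence, making all postoperative assessments impossible"
- the participant's death

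Section 2.9 adds a definition for one arm: "An adverse effect in the EG is defined as any skeletal muscle injury that occurs during (or as a result of) the training performed".

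Section 2.11 makes a per-protocol analysis the main one, restricted to women who attend at least 80% of the exercise sessions. The randomised comparison comes second: "Sensitivity analyses will be carried out using the intention-to-treat principle". Missing data are to be multiply imputed. Section 2.10 promises that the number of interruptions and their reasons will be reported.

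**The concern.** Stopping an intervention and leaving a study are different events, and section 2.10.2 treats them as one. Randomisation takes place at discharge after surgery (section 2.4), so any withdrawal during the exercise programme or later follow-up is a loss after randomisation. The primary outcome is a serum value from a fasting morning sample (sections 2.6.2 and 2.6.2.1), which most women who can no longer train could still give.

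If such women leave the study, their week-16 (T2) and 12-month (T3) values are missing because of a study rule, not because they could not be measured. Because the main analysis selects on attendance, the intention-to-treat analysis is the one place where the outcomes of women who stopped training would count. If those outcomes are imputed from women who kept training, the robustness check shares part of the selection it is meant to examine.

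**Working it through.** **The plan's own figures.** Inputs from section 2.3: difference 10 nmol/L, SD 10 nmol/L, α = 0.05 (taken as two-sided), power 85%.

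- n per group = 2 × (1.960 + 1.036)² × (10/10)² = 17.96, rounded up to 18, so 36 in total.
- With 10% loss: 36 / 0.90 = 40.
- Power at 20 per group: Φ(√(20/2) × 10/10 − 1.960) = Φ(1.202) = 88.5%.

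All three agree with the article. The withdrawal rule has no figure of its own.

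**Which grounds make assessment impossible?**

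| Ground in 2.10.2 | Rules out a blood sample at T2/T3? | Arms in which it can arise |
|---|---|---|
| Severe muscle injury | Not in itself | Both; injury caused by training only in the exercise group |
| Protocol violation (general ground) | No | Both; breach of the exercise programme only in the exercise group |
| Pregnancy during the intervention | No, but the article says it distorts the hormonal results | Both |
| Relocation | Yes, by its own wording | Both |
| Death | Yes | Both |

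For injury and protocol violation, therefore, the loss of outcome data is avoidable.

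**Effect on power.** The article gives no withdrawal rate. Assume 20 women per arm and k exercise women withdrawn, with all controls kept. Power = Φ(√[(20 − k) × 20 / (40 − k)] × 10/10 − 1.960):

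- k = 2: Φ(1.118) = 86.8%
- k = 3: Φ(1.071) = 85.8%
- k = 4: Φ(1.021) = 84.6%

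The loss from 88.5% is small. Power is not the problem.

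**Effect on the estimate.** Let the remaining exercise women have mean SHBG change m, and the k withdrawn women m − D. The mean over all 20 is [(20 − k)m + k(m − D)] / 20 = m − kD/20. An analysis that sees only m, or imputes as if D were zero, is off by (k/20) × D:

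| k of 20 | D = 5 | D = 10 | D = 20 |
|---|---|---|---|
| 1 | 0.25 | 0.5 | 1.0 |
| 2 | 0.5 | 1.0 | 2.0 |
| 3 | 0.75 | 1.5 | 3.0 |
| 4 | 1.0 | 2.0 | 4.0 |

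(nmol/L; k and D are assumptions.) A positive D flatters exercise and a negative D does the reverse. The same expression applies to withdrawn controls, and equal losses with equal D cancel in the between-group difference.

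For scale, the standard error of the difference at 20 per arm and SD 10 is 10 × √(2/20) = 3.16 nmol/L. The k = 2 row therefore runs from 0.5/3.16 = 0.16 to 2.0/3.16 = 0.63 standard errors. Two withdrawals in 20 would also use the whole 10% loss allowance in that arm.

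**The case against.** Several objections are sound, and they limit the point.

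- **The rule does not single out the exercise group.** A reader might infer that it removes exercise women selectively. The text covers any patient, and the injury ground applies whether or not the study caused the injury. A heavier loss in the exercise group is plausible but is not written into the rule.
- **Non-attendance is not a listed ground.** A reader might infer that poor attenders are withdrawn. The rule is permissive, and none of the four circumstances is non-attendance. Section 2.11 handles low attendance at analysis, and section 3.1 answers it with adherence measures. Protocol violation remains an open general ground whose intended reach cannot be told from the article.
- **Intention-to-treat analysis is not prevented.** All randomised women can be analysed as allocated with the planned multiple imputation. What changes is that the result depends on a missing-at-random assumption for the withdrawn women.
- **The article does not say that assessments stop.** Section 2.6.1 has all participants completing three assessments, and a full protocol exists that is not shown. Even so, section 2.10 is about study participation and calls these women withdrawn, so an end to assessments is the natural reading.
- **The main analysis is affected less.** An exercise woman injured before reaching 80% attendance (39 of 48 sessions) leaves the per-protocol set whatever section 2.10.2 says. Choosing an attendance-based main analysis is a separate and larger issue.

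What remains is a stated rule that, followed as written, discards outcomes the trial could collect. That is more than an omitted detail.

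**Conclusion.** The point holds as a design weakness that should be corrected. Researcher-initiated withdrawal for severe injury or protocol violation, on its natural reading, creates avoidable missing T2 and T3 outcomes, possibly more often in the exercise group. It leaves the only planned analysis that keeps the randomised groups dependent on imputation for those women.

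The size and direction of the bias are unknown. With an assumed 2 of 20 exercise women withdrawn and D between 5 and 20 nmol/L, the exercise mean shifts by 0.5 to 2.0 nmol/L against a 10 nmol/L target. This assumes arms of 20 (simple randomisation makes that approximate), no offsetting loss among controls, and an imputation model that carries no information about D. A reader might infer a bias towards exercise. That requires withdrawn women to have done worse on SHBG, and nothing in the article establishes this.

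**What to change.** In section 2.10.2, distinguish discontinuing the exercise programme from leaving the study. State that researcher-initiated discontinuation for injury or protocol violation does not end outcome collection. These women are still invited to T2 and T3, at minimum for the fasting blood sample, unless they withdraw consent or assessment is impossible. Remove protocol violation as a ground for ending follow-up.

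Leave the criteria for stopping training unchanged. Leave pregnancy outside this change as well: the article says it would distort the hormonal results, so the handling of those data should be stated separately.

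The cost is a few sentences of protocol wording. The assessments retained are already planned for every participant in section 2.6.1.

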### Statistical analysis

2.11

Despite randomization, the between-group baseline comparability will be checked. Normal distribution of continuous quantitative variables will be graphically inspected using histograms, and—when needed—normality tests will also be used. The between-group differences in the change (post–pre) in the primary and secondary effects (the main and secondary objectives 1, 2, and 3) will be analysed using a general linear model (in the case of significant deviation from normality, we will proceed with non-parametric techniques, such as quantile regression). The effect size (95% confidence interval) and the level of statistical significance will be displayed. In order to demonstrate the clinical efficacy of the supervised exercise program on ovarian function after bariatric surgery, the main analysis will be a per-protocol analysis (i.e., it will only include participants who attend at least 80% of the exercise sessions). Sensitivity analyses will be carried out using the intention-to-treat principle to check the robustness of the results. Missing data will be replaced using multiple account imputation. Despite the randomization, we will attempt to minimize potential confounding by adjusting for baseline values and other potential confounders. The association between changes in ovarian function with changes in the mechanisms involved (secondary objectives 4, 5, and 6) will be analysed using Pearson or Spearman correlations and/or regression analysis. The analyses will be conducted with Stata v.13.1 or superior (StataCorp LP, College Station, TX). Statistical significance will be set at *P* < .05.

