### Sample size

2.3

The number of patients needed was estimated based on the primary outcome—SHBG. At the time this protocol was conceived, there were no previous studies on the effects of physical exercise on ovarian function in women with severe/morbid obesity or after undergoing bariatric surgery. Therefore, the sample size was estimated using prior research on exercise effects in obese women,^[59]^ based on an expected increase in SHBG of at least 10 nmol/L in the EG compared to the CG. To detect a between-group change of 10 nmol/L (assuming a standard deviation equal to the expected effect), with a statistical power of 85% and an α error of 0.05, 36 women (n = 18 per group) will be needed. Anticipating a 10% follow-up loss, we will aim at recruiting ∼40 women. Adherence strategies will be implemented during the intervention program to minimize potential follow-up losses. If no participants are lost to follow-up, the final power of the study (with n = 40) for detecting the indicated effect would be 88.5%. In the absence of an accurate estimate for the expected standard deviation, Figure 1 represents the power curve for estimating the expected effect (the variation in the SHBG change between the EG and the CG of 10 nmol/L), considering different standard deviations and for a sample size of 36 (n ∼ 18 per group) or 40 (n ∼ 20 per group).

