##### Primary outcome

2.6.2.1

The primary study outcome is the SHBG (nmol/L) since it is a fundamental hormone for ovarian function and ovulation, is inversely related to obesity and is likely to increase with weight loss and physical exercise. It will be measured in serum and analyzed by immunoassay using the Beckman Coulter kit (ref. A48617), with a maximum value of 200 nmol/L and an inaccuracy of <7%.

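### A look at the outcome data can switch the primary SHBG analysis from a mean difference to another effect, for which the trial was not sized and which can cost power

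*Protocol article*

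**What the plan says.** Three statements in the protocol article bear on this.

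- **Default model (section 2.11).** Between-group differences in change, for the primary as well as the secondary outcomes, "will be analysed using a general linear model". The section also foresees adjustment for baseline values.
- **The check and the switch (section 2.11).** "Normal distribution of continuous quantitative variables will be graphically inspected using histograms", with normality tests added where thought necessary. Then "in the case of significant deviation from normality, we will proceed with non-parametric techniques, such as quantile regression". The section names no test, threshold or quantile.
- **What the trial is sized for (section 2.3).** The calculation is "based on an expected increase in SHBG of at least 10 nmol/L in the EG compared to the CG", "assuming a standard deviation equal to the expected effect", with 85% power and α of 0.05, giving 18 women per group. The section concedes the uncertainty in that SD: "In the absence of an accurate estimate for the expected standard deviation". No calculation covers a difference in medians or in any other quantile.

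**The concern.** The switch does more than change how a P value is obtained; it changes the quantity estimated. The linear model estimates a difference in mean change, quantile regression a difference at a chosen quantile, and a rank method something else again. When the outcome is skewed these are different numbers, so the same data could give different primary effects depending on how a histogram is read.

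The linear model's distributional assumption also concerns residuals, not the raw variables, so the check as worded looks in the wrong place.

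Finally, the trial expects about 36 evaluable women and has little power to spare. If the named fallback is less efficient than the linear model, the rule spends power that section 2.3 counts on.

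**Working it through.** **1. The plan's own figures.** Inputs from section 2.3: difference 10, SD 10, α 0.05 (two-sided reproduces the figures), power 85%.

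- n per group = 2 × (1.960 + 1.036)² × (10/10)² = 17.96, so 18.
- Power at 18: SE = 10 × √(2/18) = 3.333; 10/3.333 − 1.960 = 1.040; power 85.1%.
- Power at 20: SE = 10 × √(2/20) = 3.162; 3.162 − 1.960 = 1.202; power 88.5%.
- Loss to follow-up: 36/0.90 = 40.

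All match. They are calculations for a difference in means.

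**2. Does the switch change the effect?** Assume a log-normal variable with log SD σ and a multiplicative treatment effect. The median difference is then exp(−σ²/2) times the mean difference: 88% at σ = 0.5, 73% at 0.8 and 61% at 1.0.

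**3. Median regression under normal errors (asymptotic).** Relative efficiency is 2/π, so the effective SD is 10 × √(π/2) = 12.53.

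- At 18 per group: SE = 12.53 × √(2/18) = 4.178; 10/4.178 − 1.960 = 0.434; power 66.8%, against 85.1%.
- For 85% power: 2 × (2.996)² × π/2 = 28.2, so 29 per group.
- A rank method (relative efficiency 0.955) would keep 83.4%.

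Normal errors are, however, the case in which the switch should rarely fire.

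**4. Simulation by error shape.** 600 trials per row, 18 per group, shift of 1 SD, no baseline adjustment. Assumed: median as the quantile, default standard errors, Shapiro-Wilk on residuals at 0.05 as the trigger. Monte Carlo standard error is at most √(0.25/600) = 2 points.

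| Errors | Switch fires | Linear | Median regression | Rank test | Two-step rule |
|---|---|---|---|---|---|
| Normal | 5% | 83% | 50% | 79% | 81% |
| Laplace | 36% | 84% | 73% | 89% | 81% |
| t, 3 df | 48% | 88% | 86% | 96% | 92% |
| Log-normal, σ 0.5 | 73% | 80% | 65% | 89% | 72% |
| Exponential | 95% | 84% | 72% | 93% | 73% |
| Log-normal, σ 1 | 99% | 87% | 96% | 99% | 96% |

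With no true effect, the two-step rule rejected in 2–5% of trials and median regression in 1–4%. The low rejection rate of median regression shows that its default standard errors are conservative; 50% simulated against 67% asymptotic power under normal errors points the same way.

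**5. Simulation with baseline adjustment.** Assumed: log-normal SHBG, log SD 0.5, baseline correlation 0.6, log ratio 0.35, 18 per group, same trigger. The ranges are across separate simulations.

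| Analysis | Power |
|---|---|
| Fixed linear model | 64–66% |
| Two-step rule, median regression as fallback | 52–55% |
| Median regression throughout | 38–40% |
| Two-step rule, rank-based fallback | 67–69% |
| Fixed log-scale model | 71–75% |

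A hand check of the last row: residual SD = 0.5 × √(1 − 0.6²) = 0.40; 0.35/(0.40 × √(2/18)) = 2.63; power about 75%.

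Other settings, two-step rule against fixed linear model: 76% against 83% (log SD 0.3, log ratio 0.25), 29% against 36% (0.5 and 0.25), 23% against 33% (0.7 and 0.35). At log SD 0.5, the linear model and median regression disagreed on significance in 25–31% of trials with a true effect.

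**6. The additive case on which the trial is sized.** With a 10 nmol/L shift and normal change, the linear model had 82% power, the two-step rule 81% and the log-scale model 72–75%.

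**The case against.** The strongest objection is that the plan offers quantile regression only as an example and fixes no quantile. A rank-based method fits the wording, and with it the power loss in step 5 vanishes. This stands, and it limits the power part of the point to one permitted reading. It does not rescue the rule: a rank method also abandons the 10 nmol/L mean difference, and leaving the fallback open makes the primary effect less defined.

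Two further objections have weight. Section 2.5 blinds the analysts to allocation, which reduces the scope for steering the result, though it does not settle which effect is reported. And the exact test or threshold could sit in an analysis plan that is not shown. The point therefore rests on the switch that the article states, not on the missing detail.

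A reader might go further and infer three things that the documents do not support:

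- **That the switch is likely to fire.** The documents give no SHBG distribution, and the quantity analysed is the change. Skewed levels do not imply skewed changes.
- **That the rule costs substantial power in general.** Step 4 runs from a loss of about 11 points to a gain of about 9, and under normal errors the rule loses about 1 point.
- **That a log-scale model should be primary.** It also leaves the mean difference in nmol/L, and under the additive effect in section 2.3 it does worse than the linear model.

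**Conclusion.** The point holds in a limited form. Without any distributional assumption, section 2.11 lets inspected outcome data decide which effect the primary analysis estimates, and section 2.3 sizes the trial for only one of those effects.

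The cost in power is conditional. With median regression as the fallback and moderate log-normal skew, it is about 11–12 points (66 − 55 and 64 − 52). That figure assumes the median as the quantile, a Shapiro-Wilk trigger, log-normal SHBG with log SD 0.5 and baseline correlation 0.6, and default standard errors that account for part of the loss. False-positive risk is not the issue. This should be corrected before the data are analysed, but it does not invalidate the design.

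**What to change.** For the primary outcome, remove the normality-triggered switch from section 2.11 and name one model. For example: the between-group difference in mean SHBG (nmol/L) will be estimated by a linear model adjusted for baseline SHBG (ANCOVA), with a 95% confidence interval; residuals will be inspected, and robust or bootstrap intervals used if they are clearly non-normal. The residual check then affects only the interval, not the quantity estimated.

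Pre-specify two sensitivity analyses: quantile regression, with the quantile named, and a linear model of log SHBG reported as a ratio of geometric means.

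The cost is a sentence or two of text. Robust intervals are slightly wider, about 3–4 points of power in simulation. If the effect is truly multiplicative, the linear model gives up some efficiency to a log-scale model: 66% against 71% or 75% in the scenario of step 5. In return, the reported effect is the one the trial was sized to detect, however the histogram looks.

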**Methods::**

This is a randomized controlled trial in which ∼40 female bariatric surgery patients, aged between 18 and 45 years old, will be included. Participants assigned to the experimental group will perform a total of 48 sessions of supervised concurrent (strength and aerobic) training (3 sessions/week, 60 min/session) spread over 16 weeks. Patients assigned to the control group will receive lifestyle recommendations. Outcomes will be assessed at baseline, week 16 (i.e., after the exercise intervention) and 12 months after surgery. The primary outcome is ovarian function using the Sex-Hormone Binding Globuline, measured in serum. Secondary outcomes are serum levels of anti-mullerian hormone, TSH, T4, FSH, LH, estradiol, prolactine, and free androgen index, as well as oocyte count, the diameters of both ovaries, endometrial thickness, and uterine arterial pulsatility index (obtained from a transvaginal ultrasound), the duration of menstrual bleeding and menstrual cycle duration (obtained by personal interview) and hirsutism (Ferriman Gallwey Scale). Other secondary outcomes include serum markers of chronic inflammation and insulin resistance (i.e., C-reactive protein, interleukin 6, tumor necrosis factor-alpha, leptin, glomerular sedimentation rate, glucose, insulin and the HOMA-IR), arterial stiffness, systolic, diastolic and mean blood pressure, body composition, and total weight loss. Physical fitness (including cardiorespiratory fitness, muscular strength, and flexibility), health-related quality of life (SF-36 v2) and sexual function (Female Sexual Function Index) will also be measured.

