Other proposed mechanisms implicated in the relationship between obesity and reproductive problems, such as chronic inflammation^[53]^ or arterial stiffness,^[54]^ could also be significantly improved through exercise in this population. Recently, Stolberg et al^[55]^ found no improvement in inflammation following a training program initiated 6 months after bariatric surgery (70% women), although program adherence was clearly insufficient (i.e., only 59.4% of the participants attended 50% or more sessions) and the insufficient details about the intervention compromises replicability and the quality of the study.^[56]^ Therefore, the extent to which exercise, started immediately after surgery, can improve inflammation and arterial distensibility, and whether changes in these parameters can mediate possible improvements in women's ovarian function remain to be investigated.

For all of the above, studying the effectiveness of a supervised concurrent (strength and aerobic) exercise programme on the ovarian function of women undergoing bariatric surgery, both in the short (16 weeks) and medium (12 months) term, is of great clinical and social interest, especially considering the significant ovulatory problems that obesity confers. We postulate that a supervised evidence-based exercise program following the *Consensus on Exercise Reporting Template* (CERT),^[57,58]^ significantly improves ovarian function following bariatric surgery.

Thus, the main aim of the EMOVAR clinical trial is to examine, over the short (16 weeks) and medium (12 months) term, the effects of a supervised physical exercise program (focused primarily on aerobic and resistance training) on ovarian function in women with severe/morbid obesity who have undergone bariatric surgery, in comparison with usual care following bariatric surgery. Secondary aims are to examine the effects of the intervention on chronic inflammation and insulin resistance, arterial stiffness, physical fitness and health-related quality of life. We will also assess whether changes in inflammatory parameters, insulin resistance or arterial stiffness, induced by exercise, are associated with changes in ovarian function. Finally, the extent to which changes in body weight and composition, or changes in physical fitness (i.e., aerobic capacity and muscular strength), induced by the training program, are associated with changes in ovarian function will also be investigated.

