### Blinding

2.5

Due to the nature of the intervention (physical exercise), it is not possible to “blind” the patients, since they will inevitably know their allocation. However, the team that evaluates the primary and secondary outcomes, including the gynaecological tests, will be blinded to the patients’ allocation. The participants will receive explicit instructions not to disclose their allocation with the study staff. In addition, the data analysts will also be blinded to the patients’ allocation.

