#### Experimental group (supervised exercise; EG)

2.7.1

Patients assigned to the EG will perform a 48-session supervised physical exercise program spread over 16 weeks with a frequency of 3 sessions per week and a volume of 1 hour per session. This distribution has proven applicable in patients undergoing bariatric surgery.^[83]^ The exercise program has been comprehensively described elsewhere^[84]^ following the Consensus on Exercise Reporting Template (CERT)^[58,85]^ to maximize transparency and replicability. The exercise program will combine muscle strength and aerobic exercise in the same session (called concurrent training). Concurrent training has shown to increase weight loss and improve body composition, muscle strength, aerobic capacity and bone-mineral density to a greater extent than aerobic training and separate strength training in patients obese dieting adults.^[86]^ The exercise program will comply with international guidelines^[87,88]^ for aerobic and strength training, following criteria to progress effectively and safely.^[58]^ The training sessions will be individual and will be held in the sports facilities at the University of Almería. All sessions will be supervised^[89]^ by a Personal Trainer with a Grade in Physical Activity and Sports Sciences, and either a Master Degree in Personal Training or >2 years’ experience training obese people.

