##### Strategies to register and maximize adherence to the training program

2.7.1.1

Adherence to the exercise program will be measured throughout the intervention period on a record sheet designed *ad hoc* and completed daily by the personal trainer in each session. In addition to the attendance percentage ([no. of sessions attended/no. of sessions planned] × 100), other variables such as punctuality, physical activity outside of the program, the number and type of adverse events, and the compliance attitude during the session will also be recorded. The level of perceived effort, mood and sense of acute exhaustion induced by exercise will be recorded to try to anticipate possible symptoms (if any) of fatigue or dissatisfaction and to make pertinent adaptations (if needed). Since program adherence is essential to study the clinical effectiveness of the exercise program, strategies will be implemented to maximize it, such as sending motivational messages (each week) and videos (each month) via Whatsapp throughout the program intervention.^[84]^

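### The main SHBG analysis keeps only exercise-group women who attended at least 80% of sessions and compares them with all controls, so it is no longer protected by randomisation

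*Protocol article*

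**What the plan says.** The Statistical analysis section (2.11) gives its reason first, "In order to demonstrate the clinical efficacy of the supervised exercise program on ovarian function after bariatric surgery", and then fixes the analysis set: "the main analysis will be a per-protocol analysis (i.e., it will only include participants who attend at least 80% of the exercise sessions". It continues: "Sensitivity analyses will be carried out using the intention-to-treat principle to check the robustness of the results". It also plans multiple imputation, and adjustment for baseline values and for further confounders that it does not name.

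The sessions belong to one arm. Section 2.7.1 states: "Patients assigned to the EG will perform a 48-session supervised physical exercise program spread over 16 weeks". For the other arm the abstract states: "Patients assigned to the control group will receive lifestyle recommendations". Attendance is the share of planned sessions attended, on a record sheet "completed daily by the personal trainer in each session" (section 2.7.1.1), so it exists for the exercise group only. No matching adherence rule is given for controls.

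The Blinding section (2.5) adds that "the data analysts will also be blinded to the" allocation. The sample size section (2.3) allows for 10% loss to follow-up and makes no separate allowance for women removed for low attendance.

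**The concern.** The trial asks whether exercise plus usual care raises SHBG more than usual care alone. Concealed random allocation makes the two arms comparable. An attendance filter undoes this in one arm: the exercise women who remain are those able and willing to complete at least 39 sessions after surgery, while the controls still include women who would not have done so. If whatever governs attendance (recovery, motivation, adherence to advice generally) also governs SHBG change, the comparison mixes that difference with the effect of exercise.

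The filtered comparison is the headline result; the randomised one is demoted to a robustness check. Adjusting for baseline SHBG and other recorded covariates can reduce imbalance on what is measured, but it cannot guarantee balance on unmeasured determinants of attendance.

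There is a secondary point. Exclusions for attendance can occur in one arm only, so analysts who apply the filter, or see which women it removed, could identify the exercise group.

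**Working it through.** **1. Whom the rule can remove.** 80% × 48 = 38.4, so at least 39 sessions. Controls have no planned sessions and no attendance percentage. The workable reading is that all controls stay and only exercise-group women can be dropped.

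**2. The plan's own sample size.** Inputs from section 2.3: difference 10 nmol/L, SD 10 nmol/L, power 85%, α 0.05 (taken as two-sided, which reproduces the result).
- n per group = 2 × (1.960 + 1.036)² × (10/10)² = 17.96, so 18 per group and 36 in total.
- 36 / 0.90 = 40.
- Power at 20 per group: SE = 10 × √(2/20) = 3.162; Φ(10/3.162 − 1.960) = Φ(1.202) = 88.5%.

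The stated 36, 40 and 88.5% all reproduce by normal approximation. The calculation assumes that every woman retained is analysed.

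**3. What the filter could do when exercise has no effect.** The article reports neither the share p who will reach 80% nor the correlation r between propensity to attend and SHBG change. Both are assumptions here. If the most attendance-prone fraction p of the exercise group is kept under a normal model,

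bias = r × SD × φ(z) / p, where z is the standard normal value exceeded with probability p.

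The test compares 20p women with 20 controls, with SE = 10 × √(1/(20p) + 1/20). Two-sided type I error comes from the noncentral t distribution with shift bias/SE. SD is held at 10 in the selected group, which is an approximation.

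| p | r | Bias (nmol/L) | SE | Type I error |
|---|---|---|---|---|
| any | 0 | 0 | – | 5.0% |
| 0.90 | 0.3 | 0.3 × 10 × 0.1755 / 0.90 = +0.6 | 3.25 | 5.4% |
| 0.80 | 0.1 | 0.1 × 10 × 0.2800 / 0.80 = +0.35 | 3.35 | 5.1% |
| 0.65 | 0.3 | 0.3 × 10 × 0.3704 / 0.65 = +1.7 | 3.56 | 7.5% |
| 0.90 | −0.3 | −0.6 | 3.25 | 5.4% |
| 0.65 | −0.3 | −1.7 | 3.56 | 7.5% |

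With negative r the excess rejections favour control, and a real benefit would be understated.

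**4. Power with intention-to-treat as the main analysis.** If 10 nmol/L is the effect of assignment, step 2 is unchanged. If it is the effect in attenders and the others gain nothing (assumption), the effect is diluted, at 20 per group:
- 80% attending: 8 nmol/L; Φ(8/3.162 − 1.960) = Φ(0.570) = 72%.
- 70% attending: 7 nmol/L; Φ(7/3.162 − 1.960) = Φ(0.254) = 60%.

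**5. Whether the 80% cut-off can define treatment in an instrumental-variable analysis.** A woman with 30 of 48 sessions falls below the cut-off but received much of the programme. Suppose 65% reach 80% and gain 10 nmol/L, and the rest gain 5 (assumptions). The effect of assignment is 0.65 × 10 + 0.35 × 5 = 8.25. Dividing by 0.65 gives 12.7 nmol/L instead of 10. Allocation then affects SHBG among women counted as untreated, which breaks the exclusion restriction.

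**The case against.** The strongest defence is that the choice is open and reasoned: the authors want efficacy under adequate exposure, intention-to-treat is prespecified, covariate adjustment is planned and CONSORT reporting is promised. A randomised estimate is therefore planned, and it would be wrong to infer that the trial will have none. Per-protocol power also holds up better on paper: if 80% of the exercise group are kept (16 against 20) and attenders gain 10 nmol/L, it is 84.6%, against 72% for diluted intention-to-treat. But that power attaches to a comparison that does not identify efficacy, because attenders and all controls differ by more than exercise.

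Some stronger inferences are tempting and are not supported.

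- **That the bias favours exercise.** This is plausible, since the article expects SHBG to rise with weight loss. But it reports no association between attendance and SHBG change, and it cites a post-bariatric trial in which exercise changed insulin sensitivity but not weight loss.
- **That attendance will be poor.** The Introduction says of an earlier post-bariatric trial that "only 59.4% of the participants attended 50% or more sessions". That concerns a 50% threshold in a programme started 6 months after surgery, whose adherence the article criticises. Here sessions are individual and supervised, with adherence strategies, so the figure does not supply p.
- **That the rule deletes every control.** This follows only from reading a condensed sentence literally, and nobody would implement it.
- **That the analysts will be unblinded.** Someone else could prepare a coded, filtered dataset. Unequal arms alone reveal little under simple randomisation: with 40 women the arms differ by 4 or more with probability 1 − 0.125 − 2 × 0.119 = 0.64.

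**Conclusion.** The concern holds as a design fault in the main analysis. A post-randomisation filter that can act on one arm only decides who enters the headline comparison of a superiority trial, and nothing elsewhere in the article restores the randomised comparison for that result. This conclusion needs no assumed figure.

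The amount of bias does. It is zero if attendance is unrelated to SHBG change. In the illustrations at r = 0.3 it is 0.6 to 1.7 nmol/L, or 6% to 17% of the 10 nmol/L target, with type I error of 5.4% to 7.5%, and it has the opposite sign if r is negative. These figures rest on assumed p and r, SD 10 and 20 per arm, and they are not forecasts. Loss of analyst blinding is a possibility that depends on who handles the attendance data. The sample size arithmetic is correct as stated.

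**What to change.** Make intention-to-treat the main analysis: all randomised women in their allocated group, SHBG change adjusted for baseline SHBG, with the planned multiple imputation. Keep the 80%-attendance analysis as supportive, state that it filters the exercise group only, and have someone other than the blinded analysts apply the filter.

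If an efficacy estimate is wanted, use allocation as the instrument with the number of sessions attended, or any attendance, as the treatment variable. Do not use the 80% cut-off, for the reason in step 5 of the working. A sessions-based estimate needs an assumption about how effect relates to dose, and either version will be imprecise with about 40 women.

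Cost: no new data, but a documented amendment, because version 1.0 has ethics approval and enrolment was set to begin on 15 October 2019. The authors should also say whether 10 nmol/L is the effect of assignment or the effect in attenders. In the first case 88.5% power at 20 per group stands. In the second, with no gain in non-attenders, power is about 72% at 80% attendance and 60% at 70%, and that trade-off should be stated openly.
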